## Secondary Objectives

To determine if 8 weeks of stand-alone RT compared to control, (AIT) improves mental (functioning, mental health symptoms) and physical health outcomes

To investigate comparisons of psychological responses to a single session of exercise (week 3 and 8) between exercise conditions, RT and AIT

To correlate preference for exercise condition (RT or AIT) prior to randomisation with subsequent adherence.

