### Secondary

Comparison of stand-alone RT with control, aerobic interval training(AIT) with respect to mental (functioning, mental health symptoms) and physical health outcomes

Allocation to exercise condition the participant expresses preference for prior to randomisation will result in increased adherence.

Comparison of psychological responses to a single session of exercise (week 3 and 8) between exercise conditions, RT and MIIT will be identified

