## Statistical Analysis

Data analyses will be conducted using SPSS Statistics 24, (SPSS Inc, Chicago, Illinois) for the primary outcomes. Continuous variables were summarized using means and standard deviations (SD) (or median and interquartile range for non-parametric data). All variables will be tested for normality using the Shapiro-wilks test, and visual inspection of Q-Q plots. Baseline demographic and clinical variables, participation and AE rates and mean aggregate acceptability scores will be compared between the two exercise groups using independent t-tests or Mann-Whitney U for non-parametric data. Chi square analysis for categorical data will be used to detect any baseline differences between the two exercise groups and for comparison of acceptability categories (strongly agree/agree versus other) per questionnaire item between the groups.

Baseline demographic and clinical variables will be compared between the 2 exercise groups using independent t tests (or Mann Whitney U tests if data non parametric) for continuous data and Chi2 square analysis for categorical data to detect any baseline differences between the 2 exercise groups. Baseline characteristics of those who complete >50% of the program will be compared to those who withdraw to identify characteristics of those who drop out.

To analyse the impact of the proposed exercise intervention on secondary outcomes, analyses will be performed on an intention-to-treat basis. Change from baseline in secondary outcomes at week 8 will be calculated as least squares (LS) means using a Linear Mixed Effects Model (LMM). Treatment group (RT or AIT) and time will be used as factors, with covariates established in previous similar research (age, gender, participation, and antipsychotic medication use),(García-Garcés et al., 2021b). Where group/time differences were detected, posthoc (Bonferroni) analyses will be carried out separately for the intervention and control group, with Cohen’s d estimate of effect sizes provided. LMM was performed using R (software version 4.04, 2024). All the statistical tests were two-tailed with the critical P value for significance set at?<?0.05.

For the RT group only, 12 RM strength will be assessed for normality and compared pre and post the intervention using paired samples t test.

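### The follow-up tests and effect sizes for secondary outcomes are within-arm, behind an ambiguous trigger, although the objective is RT compared with AIT

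*Protocol*

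**What the plan says.** The question is between arms. Protocol section 2.2 opens the relevant objective with "To determine if 8 weeks of stand-alone RT compared to control" and asks whether mental and physical health outcomes improve. Section 11.2.2 lists as an endpoint the "Comparison of stand-alone RT with control, aerobic interval training(AIT) with respect to mental" and physical health.

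Section 11.4 gives the analysis. Change from baseline at week 8 is to come as least squares means from a linear mixed model, on an intention-to-treat basis: "Treatment group (RT or AIT) and time will be used as factors", plus covariates. The next step is conditional: "Where group/time differences were detected", then "posthoc (Bonferroni) analyses will be carried out separately for the intervention and control group", "with Cohen’s d estimate of effect sizes provided". Tests are two-sided at 0.05.

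For these outcomes the section names neither a group-by-time interaction nor an RT-minus-AIT contrast.

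**The concern.** Outcomes are assessed at baseline and week 8 only (section 3; SEES has its own analysis). A post hoc analysis run separately in each arm can therefore only compare week 8 with baseline in that arm. Two such p-values do not compare RT with AIT, because one can fall below 0.05 and the other above it when the arms changed equally. A Cohen's d attached to this step describes change in one arm, which mixes any treatment effect with natural course, practice and regression to the mean.

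The trigger adds to this. Both arms receive supervised moderate-intensity exercise matched for volume, at a weekly amount that section 7.1 links to better mental health. Improvement over time in both arms is what the protocol itself would expect. If that time effect counts as a group/time difference, the per-arm tests open even when RT and AIT are equivalent.

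At stake is the comparative message on WHODAS 2.0, BPRS, SANS, BREQ-3 and the physical measures, and the between-arm estimate that a later trial would want.

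**Working it through.** **Inputs from the protocol.** The target is 50 participants, about 25 per arm, with 20% dropout (section 11.3). Completers per arm: 50 × (1 − 0.20) / 2 = 20. Alpha is 0.05, two-sided (section 11.4). The protocol states no power or error rate for these outcomes, so there is no figure of its own to reproduce.

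**Assumption.** The same true change d in both arms, in units of the SD of change. The protocol gives no effect size or SD, so d is shown over a range.

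**Step 1: both within-arm tests always run.** Let p be the power of a paired t-test with n = 20, from the noncentral t with noncentrality d√20. The arms are independent, so P(exactly one arm significant) = 2p(1 − p), and RT alone is half of that. At d = 0.45, p = 0.480 and 2 × 0.480 × 0.520 = 0.499. This expression cannot exceed 0.50, and d = 0.45 sits almost at that peak, so it is not a typical value.

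**Step 2: add the trigger.** With two time points and complete data, and leaving covariates aside, the interaction test is a two-sample t-test on change, and the time test is a t-test of the average change in the two arms. Trials were simulated with 20 per arm and equal true change. A split verdict was counted only when the trigger was met at 0.05.

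| d | p per arm | Split verdict, no trigger | Split verdict, time effect opens it | Split verdict, interaction required |
|---|---|---|---|---|
| 0.2 | 0.136 | 23% | 15% | 4% |
| 0.3 | 0.247 | 37% | 29% | 4–5% |
| 0.45 | 0.480 | 50% | 46% | 5% |
| 0.6 | 0.721 | 40% | 39% | 4% |
| 0.8 | 0.924 | 14% | 14% | 2% |

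RT alone is significant in half of each figure. For example, at d = 0.45 it is 23% with the time trigger and about 2% with the interaction trigger.

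**Step 3: Bonferroni.** Section 11.4 does not define the family. Taking 0.025 per arm as an assumption and d = 0.5, p = 0.439 and 2 × 0.439 × 0.561 = 0.493 without a trigger. With the time trigger it is 48%. Dividing alpha only moves the value of d at which the peak occurs.

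**Step 4: the between-arm contrast.** Under equal true change, the difference in change is significant in 5% of trials at every d, about 2.5% in RT's favour.

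**The case against.** The strongest reply is that group/time is ordinary shorthand for the group-by-time interaction, and that simple effects per arm are the usual follow-up to a significant one. On that reading the interaction test is the RT-versus-AIT comparison, and the per-arm step only describes which arm moved. Split verdicts under equal change then fall to about 2–5%. The model also contains treatment group and yields least squares mean changes, so a between-arm estimate can be obtained from it.

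Much of this stands. A reader might infer that the plan contains no between-arm test at all. The text does not support that: the interaction reading is plausible, and the model can supply the contrast. What can be said is that the wording never names it.

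Two things survive. First, the literal text lists group and time as factors and makes differences in group/time the trigger, so a time effect alone can be taken to satisfy it. Second, even on the favourable reading, the follow-up inference and the effect size that the protocol specifies are within-arm, and a non-significant interaction leaves no stated between-arm estimate or interval. An analysis plan may add detail, but what this protocol does fix points at a different contrast from the one in sections 2.2 and 11.2.2.

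It is also fair that the only stated hypothesis (section 11.1) concerns feasibility and acceptability. How a split result would be presented is not known.

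**Conclusion.** The concern holds in a limited form. Section 11.4 attaches its post hoc tests and Cohen's d to change within each arm, while the objective and endpoint are between arms, and the trigger for those tests can be read in two ways. With 20 completers per arm, equal true change and two-sided 0.05, a split verdict arises in about 29%, 46%, 39% and 14% of trials at 0.3, 0.45, 0.6 and 0.8 SD if a time effect opens the tests. It arises in about 2–5% if the interaction must be significant. The effect sizes are assumed.

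It may be tempting to say that half of such trials would give a split verdict and a quarter would wrongly favour RT. That ignores the trigger and uses an effect size near the maximum of 2p(1 − p), so the document does not support it as a general figure.

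The consequence is confined to secondary outcomes of an exploratory trial whose primary outcome is feasibility. The wording should be corrected, but it does not threaten the primary result.

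**What to change.** In section 11.4, state that the model includes the group-by-time interaction. State also that the result for each secondary outcome is the between-arm difference, RT minus AIT, in change to week 8, with a 95% CI and a standardised between-arm effect size, reported whether or not the interaction is significant. Show within-arm changes with intervals as description only, and say that they are not evidence that the arms differ.

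The cost is a few sentences in section 11.4, repeated in any analysis plan. The data and the mixed model are the same and there are fewer tests. Sample size, visits and procedures are unaffected.

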**Measures include:**

1. WHODAS 2.0 –a reliable and valid assessment instrument for health and disability in all adult populations across different cultures, which covers six domains of functioning including cognition, mobility, self -care, getting along, life activities and participation. It is a 36 item questionnaire and will be interviewer administered.
2. Psychiatric symptoms will be measured using the Brief Psychiatric Rating Scale (BPRS) through the use of a semi-structured interview guide and an anchored scoring version of the BPRS-A. The BPRS was developed for efficient and comprehensive assessment of change across a broad range of psychiatric symptoms, is brief, reliable and sensitive and has been used extensively across a variety of settings and patients (1, 2).
3. Negative symptoms will be measured by the Scale Assessment of Negative Symptoms (SANS), a reliable and valid scale, using the Interview guide for Assessment of Negative symptoms (IG-SANS) (53-55).
4. Motivation to exercise; The Behavioural Regulation in Exercise Questionnaire (BREQ3) is a 24-item questionnaire used to assess amotivation, and external, introjected, identified, integrated and intrinsic behavioural regulations for exercise (four questionnaire items for each behavioural regulation subscale). Scoring is on a 5-point Likert scale ranging from 0 ('Not true for me') to 4 ('Very true to me'). BREQ-3 has high test-retest reliability (ρ>0.7) and has been shown to be moderately predictive of exercise participation (56).
5. Physical capacitywill be measured using three tests; the six-minute walk test (6MWT), which is a submaximal test to assess functional capacity that is commonly used for adults with mental illness (3). The 6MWT involves the participant walking as far as possible back and forth along a flat 20 m surface in six minutes; the tester provided standardised encouragement every minute consistent with guidelines (4).

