To examine the association between exercise preference prior to randomisation with participation, a one-way ANOVA compared exercise participation rates between three groups; (i) those who randomly received their exercise preference, (ii) those who did not, (iii) those who expressed no exercise intervention preference.

The three feeling state domains from the SEES would be assessed using a group (RT, MIIT), time (pre/post) ANOVA with repeated measures. The effect size of the differences between values will be interpreted using Cohen’s *d* statistic ([Cohen, 1988](https://journals-humankinetics-com.ezproxy.library.uq.edu.au/view/journals/japa/27/3/article-p325.xml" \l "r8)). An effect size of <0.2 reflects a negligible difference; ≥0.2 to ≤0.5, a small difference; ≥0.5 to ≤0.8, a moderate difference; and ≥0.8, a large difference.

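### Every secondary outcome is tested at p<0.05 with none ranked, and the only correction applies to within-arm follow-ups, in a trial sized for feasibility alone

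*Protocol*

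**What the plan says.** The secondary objective (Protocol, section 2.2) is comparative and is worded as a question to be settled: "To determine if 8 weeks of stand-alone RT compared to control, (AIT) improves mental (functioning, mental health symptoms) and physical health outcomes". Section 11.2.2 repeats the RT-versus-AIT comparison. Neither section names a key outcome or an order.

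Section 11.4 gives the analysis: "Change from baseline in secondary outcomes at week 8 will be calculated as least squares (LS) means using a Linear Mixed Effects Model (LMM", with arm and time as factors. I read this as one model per outcome. When a group/time difference is found, "posthoc (Bonferroni) analyses will be carried out separately for the intervention and control group", with Cohen's d provided. This is the only multiplicity adjustment in the document. The threshold covers all tests: "All the statistical tests were two-tailed with the critical P value for significance set" at 0.05.

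The three SEES domains go through a repeated-measures ANOVA. In the same paragraph d is read by fixed bands, starting with "An effect size of <0.2 reflects a negligible difference" and moving through small and moderate to large at 0.2, 0.5 and 0.8. No interval is mentioned.

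Sections 2, 3 and 11.3 call the trial exploratory, with feasibility as the primary outcome. Section 11.3 bases the 50 participants (about 25 per arm, 20% dropout) on available resources. It gives no effect size, SD or power for any secondary outcome.

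**The concern.** The objective and the significance rule promise answers that the design was not built to give. A p-value below 0.05 on one of many unranked outcomes would count as significant under section 11.4. Nothing in the document tells the reader to treat it as descriptive.

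The Bonferroni step does not help, for two reasons. The mixed-model outcomes are measured only at baseline and week 8, so on the natural reading each arm has a single pre-post contrast per outcome; correcting that contrast leaves the number of outcomes untouched. And a change within one arm is not the RT-AIT difference. One arm can show a significant change and the other not, while the arms barely differ.

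At stake is how the secondary results on symptoms, function and fitness are read, and whether a chance finding is carried forward as a reason to prefer one type of exercise.

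**Working it through.** **The plan's own figure.** There is no power calculation to reproduce. The target is consistent with itself: 2 x 25 = 50, and 25 x (1 - 0.20) = 20 completers per arm.

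**Counting the tests** (Protocol section 6 and Table 1; a derived count, not a stated one):
- WHODAS 2.0, BPRS and SANS: 3. WHODAS counts once, although it is described as an instrument "which covers six domains of functioning including cognition, mobility, self -care, getting along, life activities and participation".
- Six-minute walk, sit-to-stand, grip and push-ups: 4.
- Systolic and diastolic blood pressure, weight, waist and BMI: 5.
- SEES domains: 3, not doubled for weeks 3 and 8.
- BREQ-3 subscales: 6, if each is tested.

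Totals: 3 + 4 + 5 + 3 = 15 without BREQ-3, and 15 + 6 = 21 with it. The acceptability items, adverse-event and participation comparisons and the preference ANOVA are left out; they would raise the figures below.

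**Chance of at least one p<0.05 with no true differences.** For m independent tests this is 1 - 0.95^m: 1 - 0.95^21 = 65.9% and 1 - 0.95^15 = 53.7%. Outcomes are in fact correlated, and the document gives no correlations, so the other columns are simulations (200,000 to 300,000 draws) under assumed values. *Grouped* means 0.4 to 0.9 within a family of measures and 0 to 0.3 between families.

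| Tests | Independent | Grouped | Common 0.3 | Common 0.5 |
|---|---|---|---|---|
| 21 | 65.9% | 59.0% to 52.4% | 55.5% | 42.8% |
| 15 | 53.7% | 46.8% to 42.2% | 45.8% | 35.9% |

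The expected number of false positives does not depend on correlation: 21 x 0.05 = 1.05, or 15 x 0.05 = 0.75.

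**The SEES labels.** Section 11.4 does not say whether d compares arms or compares pre with post. If it compares arms, its standard error with no true difference is about sqrt(2/n):
- 25 per arm: sqrt(2/25) = 0.283. P(|d| >= 0.2) = 48% and P(|d| >= 0.5) = 8% (t distribution, 48 df). The 95% interval is about d +/- 0.57.
- 20 per arm: sqrt(2/20) = 0.316. P(|d| >= 0.2) = 53% and P(|d| >= 0.5) = 12% (38 df). The 95% interval is about d +/- 0.64.

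The interval on either side is wider than the whole distance from zero to the moderate cut-off of 0.5.

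**The case against.** The strongest reply is that the trial says it is exploratory. The only hypothesis, in section 11.1, concerns feasibility and acceptability, and the pre-set thresholds in section 3 are feasibility criteria. Such a trial need not control familywise error over secondary outcomes. That stands, and no such control is asked for here. But the label does not cancel the significance threshold or the wording of section 2.2, and nowhere are secondary p-values called descriptive.

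A second reply is that ranking, multiplicity and intervals usually belong in a statistical analysis plan, which is not at hand. True of anything the Protocol leaves open. But the threshold, the within-arm correction, the effect-size bands and the objective are stated in the Protocol itself.

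Third, the count is constructed. BREQ-3 measures motivation to exercise, which is not among the functioning, symptom or physical outcomes of the main secondary comparison, and no text says its subscales are tested one by one. Weight and BMI are close to one test over 8 weeks. This stands, and is why the count and the probability are given as ranges.

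Fourth, the bands are conventional descriptions of size, not a decision rule, and they stand in the SEES paragraph. For the mixed-model outcomes d is given only where a difference was detected. If the SEES d is within person, its standard error depends on the pre-post correlation and the figures above do not apply. This also stands, so the label calculation is confined to SEES and is conditional.

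Finally, the Protocol does not state which comparisons the Bonferroni step covers. One pre-post contrast per arm is the natural reading of two time points, but it remains a reading.

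**Conclusion.** The point holds as a mismatch between stated rules and stated purpose. All secondary outcomes are tested at two-sided 0.05 without ranking, and the only correction is aimed at within-arm follow-ups that do not answer the RT-AIT question. With no true differences, at least one p<0.05 would appear with probability of roughly 42% to 66%. This rests on 15 to 21 tests and on correlations from none to the grouped pattern assumed above. A common correlation of 0.5 gives 43% with 21 tests and 36% with 15. For SEES, if d is between arms with 20 to 25 per arm, a label of small or larger arises by chance in about half of comparisons.

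A reader might go further and infer that the trial will usually report a false difference. The documents do not support that: the figure falls below one half with the smaller count or with stronger correlation. Nor do they support saying that every secondary outcome will carry a verbal effect-size label, or that RT will be declared effective on one significant result. The feasibility criteria and the sample size are not affected.

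**What to change.** In section 11.4:
- Report each secondary outcome as the RT-AIT difference in change from baseline with its 95% CI, in place of the within-arm significance follow-ups. The planned mixed model can supply this estimate.
- State that the secondary analyses are exploratory and that no benefit will be concluded from p<0.05 on any single one.
- Show d only with its CI, and say whether it is between arms or within person.

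In section 2.2, change the opening of the first secondary objective to *To estimate*.

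A Bonferroni correction across outcomes is not the better route. With 21 tests it would need p < 0.05/21 = 0.0024. Even at 0.05, power for a true d of 0.5 is only about 35% with 20 per arm and 42% with 25 (normal approximation).

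The cost is wording. The trial gives up nominal significance claims on secondary outcomes; recruitment, data collection and the feasibility endpoint stay as they are.

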# Data Management

A screening log will be utilized to track potential participants and also record the counts of individuals approached, consented, meeting inclusion/exclusion criteria, withdrawals, and completion (in keeping with standard CONSORT diagram requirements).

The Case Report Form (CRF) will comprise of the hard copy questionnaires, clinical assessments and measures. These de-identified data will be retained in a secure room, in a locked filing cabinet at Queensland Centre for Mental Health Research.

De-identified data from the CRFs will be entered into a spreadsheet that is stored on a password protected Queensland Health computer, which only members of the research team will have access to. Delegated research assistant will be trained in, and responsible for, entering data into the database. A copy of the PICF will be stored in a secure room in a locked filing cabinet separate from the CRFs at Queensland Centre for Mental Health Research.

All data will be exported into SPSS software to enable statistical analysis.

GENEActiv accelerometer data will be downloaded at completion of baseline and analysed in Matlab 2016a (The MathWorks, Inc., Natick, Massachusetts, United States) on a password protected Queensland Health computer.

# Monitoring and Quality Assurance

The investigator will submit to the Reviewing HREC, annual (or more frequent if requested) reports of the study.

The investigator will monitor data entered and be responsible for resolving data entry errors and discrepancies.

Data quality will be ensured by performing data entry checks for consistency between the CRF and the data entry into the password protected spreadsheet. These checks will be performed during data entry so that discrepancies can be resolved immediately.

# Investigator Responsibility

The Coordinating Principal Investigator will be responsible for the conduct of all aspects of the study. The study and its associated documents will be reviewed and approved by the appointed certified HREC and Research Governance before study start.

Prior to submission to appointed HREC and Research Governance, the investigator will sign the protocol signature page confirming her agreement to conduct the study in accordance with the protocol, GCP and other regulatory requirements locally applicable. All relevant data and records will be provided to the HREC as required.

Each Investigator will comply with the local regulations regarding clinical trials and the Investigator responsibilities outlined in the ICH GCP guidelines.

